#### 4.13 Monitoring and supervision

Currently, CHWs are visited by RHC staff and the Mobile and Outreach Team from CHS. The visits are supposed to be monthly but are often not this frequent. Some RHC staff instead invite CHWs in their catchment area to the health facility on a regular basis to assist with the work at the facility. During these visits the RHC staff provide support to the CHWs and go through their records. Both methods for providing support to CHWs and supervise their work will be maintained and encouraged in all the study areas. The supervisory visit to CHWs will be linked with the outreach service, which provides immunization, and growth monitoring services to these communities. The DHMT and CHS will facilitate the supervisory visits through the outreach services. During these visits the team will check on the CHW’s routine records of consultations and referrals, as well as medications, supplies and other logistical issues. Restocking of the CHW’s drug supplies will also occur at these visits.

Every three months (the quarterly visit), the health center team will spend a little more time with the CHW in order to undertake some performance assessment.

The NHCs and the HCCs will be encouraged to support and supervise the work of the CHWs. These committees are local structures set up to support community-based agents and health workers for implementation of health programs. They are responsible for initiating and supporting developmental activities and mobilizing communities and local resources to improve household and community health.

#### 4.14 Follow-up

The patients seen by the CHWs with fever and/or fast breathing will be followed up at home by the data collectors to assess the outcome of the treatment given or recommended. The follow-up visit will occur 5-7 days after the visit to the CHW. The data collectors will make contacts with CHWs at least every other day to take particulars of children treated from the identification and baseline forms in order to schedule a follow-up visit. During the follow-up visits, the data collectors will interview the caregiver (the person who took the child to see the CHW or in his/her absence a family member who knows sufficiently about the illness and the care received); and perform some basic examination including taking of temperature and counting of respiratory rate. Information that will be collected during the follow-up visits will include, complaints that prompted heath seeking at the CHW, treatment given, counseling or advice given, referrals, self-reported adherence to the medication, outcome of the visitation, alternative treatment after the visit and where such alternative treatment was obtained and current general condition and complaints. They will also be asked questions to explain inappropriate treatment. If a subject is found not to be improving, the data collector will advise the caregiver to go to the clinic.

#### 4.15 Community mobilization and sensitization

During the initial months of the study, we will conduct a series of meetings with key decision makers and community leaders in the study area as part of efforts to mobilize awareness and support for the study. These community outreach and sensitization meetings will inform the community about the existence and purpose of the study as well as the benefits not only to their communities but also to the country and Africa at large. The reasons for choosing the area and the proposed design will be explained to them. Community leaders will be given the opportunity to decide whether they want their communities to participate in the research. Communities whose leaders oppose to the research will be excluded by not enrolling CHWs working in these communities. Central to this process will be the NHCs, and the chairpersons for each committee. Information will first be disseminated via the chairpersons, and then expand to include local meetings for each committee, and thence to the wider communities that they serve. These activities will also attempt to generate local support for the study and the role the community is expected to play to ensure the success of the study.

#### 4.16 Counseling and Community education

CHWs will provide counseling and basic health information to their patients during consultation. The counseling will include the need to return if condition deteriorates or the child experiences any adverse effects of the treatment. In addition, the CHWs in collaboration with the existing community based health educators in the area: NHCs, CPTs, child survival facilitators; community based distributors; traditional birth attendants and growth monitors will provide basic health information to the communities. Elements of such messages will include:

- General danger signs requiring immediate referral to a health facility
- Symptoms of pneumonia and malaria requiring assistance from the CHW, including danger signs
- Need to use the services of the CHWs
- Importance of adhering to counseling and instructions
- Information about taking the drugs themselves, side effects, need to take with food
- Preventive measures to be used with regard to malaria and pneumonia

#### 4.17 Adverse events

Adverse events from the use of drugs will be tracked in both the intervention and the control arms. Adverse events attributable to the use of RDTs, such as severe bruises, skin infections, and prolonged bleeding following finger pricks will also be tracked in the intervention arm. This will be done at both the CHW and health center levels. Caregivers will be counseled to report any adverse event immediately to the CHW or any nearest health facility. At the CHW, an adverse event form will be filled and the patient referred after which the data supervisor will be informed accordingly. At the health facility level the attending health personnel will manage the patient accordingly, complete the adverse event form and inform the supervisors. The supervisor will report to the Study Coordinator who will review the case and form and report any serious adverse event to the study oversight committee and the data safety monitoring board (DSMB).

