**3.6 Other Outcome Variables**

- Proportion of negative RDT cases which receive ACTs from CHW or another malarial treatment from another source.
- Proportion of negative RDT cases with fast breathing and treated for pneumonia.
- Proportion of children with fast breathing whose symptoms and signs resolve without antibiotics.
- Proportion of children with pneumonia referred who comply with referral within 24 hours
- Proportion of children who experience adverse events attributable to the use of RDTs, such as severe bruises, skin infections, and prolonged bleeding following finger pricks
- Proportion of sick children correctly classified by CHW
- Proportion of sick children prescribed appropriate treatment for malaria/pneumonia according to the treatment algorithm
- Proportion of children treated for malaria/pneumonia who experience adverse events
- Proportion of drug and/or RDTs supply properly accounted for (consistency between stock in hand from stock summary forms and stock consumed based on consultation/treatment forms)
- Proportion of caretakers who take children to a CHW or health facility within 24/48 hours of onset of fever and or cough/difficult breathing.

.

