**4.11.1 Rationale for choosing Amoxicillin**

The decision to use amoxicillin was made in conjunction with the IMCI unit of the Zambian MOH. We chose amoxicillin based on the comparative therapeutic advantages and disadvantages of several candidate antibiotics, local patterns of use, and restrictions on the categories of antibiotics that can be used in community settings according to current Zambian health policies. It is one of the drugs recommended by the Zambia National treatment guidelines for pneumonia. Amoxicillin has a long safety record, is readily available in Zambia, is inexpensive, widely accepted by patients and clinicians, and has excellent bioavailability when taken orally.

The very few serious side effects to amoxicillin that occur are due to hypersensitivity. Since it will be given in an oral form, this form of reaction is not anticipated. Less acute reactions, respiratory and skin manifestation including tightness in the chest, itching and urticaria rash may occur and we will look out for them.

We are considering the use of tablets over syrups as tablets offer advantages over the syrup, which include lower cost, easier dosing, easier ability to comply, and ease of packaging and distribution.

Treatment Chart

| Weight | Age | Dose | Total dose |
| --- | --- | --- | --- |
| 4-9 kg | 6-11 months | ½ tab 3x/day  5ml (1tsp) 3x/day | 4½ tabs  45 ml |
| 10-19 kg | 12 m – 5yrs | 1 tab 3x/day  10ml 3x/day | 9 tabs  90 ml |

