The data collectors will visit the CHWs at least every other day to collect completed identification and baseline forms to schedule a follow-up visit. The DC will check with the CHW register to ensure that every child seen by the CHW with fever of fast breathing has a completed identification and baseline form. The follow-up visits will be made at 5-7 days after the caregiver visits the CHW. Information that will be collected during the Day 5 – 7 follow-up visits will include, complaints that prompted heath seeking at the CHW, whether rapid diagnostic test was done, treatment given, counseling or advice given, self-reported adherence to the medication, outcome of the visitation, alternative treatment after the visit and where such alternative treatment was obtained, current general condition and complaints and results of temperature and respiratory rate taken.

Economic cost data from health facilities will be collected by the data collectors. These data will include the average costs associated with treating uncomplicated and severe cases of malaria and pneumonia, including overhead, equipment, personnel, medicines, and supplies. This information will then be matched with the case records in order to estimate the facility-based costs of treatment for children in intervention and control groups.

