**9.0 POTENTIAL RISKS/DISCOMFORTS AND BENEFITS**

**9.1 Potential Risks/Discomforts to CHWs**

The CHWs' participation in the study may pose additional risk beyond what they would normally experience occupationally. The misuse or the perception of misuse of medication or misclassification could cause their reputation to be tainted or harmed in the community. This will be minimized through regular performance assessment and providing feedback to the CHWs. There is also the risk of pricking themselves during the performance of RDT. This will be minimized by emphasizing the need not to rush and to use extreme care when handling sharp objects and also how to dispose off sharp objects during the training. They will also be taught what to do in the event of them pricking themselves.

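### Adverse events reach the study only by caregiver report to a CHW or facility; the day 5-7 home visit lists no adverse-event question, so the section 3.6 proportions are likely to be undercounted by an unknown amount

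*Protocol*

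**What the plan says.** Section 3.6 names two adverse-event proportions as outcome variables. One concerns drugs: "Proportion of children treated for malaria/pneumonia who experience adverse events". The other concerns finger-prick events attributable to the RDT, such as bruising, skin infection and bleeding. Section 4.11.1 says of milder amoxicillin reactions that "itching and urticaria rash may occur and we will look out for them".

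Section 4.17 fixes where and how events are found: "This will be done at both the CHW and health center levels. Caregivers will be counseled to report any adverse event immediately to the CHW", with the nearest facility as the alternative. The CHW or the attending facility worker then completes the adverse event form and informs the supervisor, who reports to the study coordinator. Data collectors do not appear in this section.

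The day 5-7 home visit is described twice. Section 5.1 lists, among other items, "whether rapid diagnostic test was done, treatment given, counseling or advice given, self-reported adherence to the medication, outcome of the visitation", followed by alternative treatment, current condition and complaints, temperature and respiratory rate. Section 4.14 gives a similar list and adds: "If a subject is found not to be improving, the data collector will advise the caregiver to go to the clinic".

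**The concern.** The protocol sends a trained data collector to the home within a week of treatment to interview the caregiver and examine the child, but does not use that visit to ask about adverse events. The numerators of the section 3.6 proportions then come only from caregivers who took the trouble to report, while section 3.6 words the drug proportion over children treated. A rash that faded, or a finger that bled and healed, may leave no trace.

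Sections 2 and 4.1 give reasons to expect under-reporting: care seeking at facilities is described as suboptimal, roads are poor, and some villages are cut off for at least two months a year. Section 9.2 rates the intervention as more than minimal risk and notes that CHWs are not used to prescribing these drugs, so a low observed rate could be read as reassurance that the data do not provide.

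Two other parts of the plan draw on the same route. A drug-related serious adverse event is one component of treatment failure (section 3.5), which is the health outcome of the economic analysis (section 4.18), and section 4.17 supplies serious events to the DSMB.

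**Working it through.** The protocol gives no adverse-event rate, reporting fraction or safety sample size, so there is no figure to reproduce. The check sets the sections side by side.

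1. **Can any written route other than 4.17 find an event?**
   - Home visit (4.14, 5.1): no adverse-event item. The nearest items are current condition and complaints, and alternative treatment since the CHW visit.
   - CHW register, monthly CHW form and monthly facility form (5.1): no adverse-event item.
   - Household surveys (5.1): no adverse-event item.
   - Monthly supervisory review (9.2): covers cases and referrals, so it would not find a child who never returned.

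   No other route asks for adverse events.

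2. **What can the home visit pick up as described?**
   - Event still present on day 5-7: probably, as a current complaint.
   - Resolved event that was treated elsewhere: possibly, as alternative treatment.
   - Resolved event that was not treated: no listed item covers it.

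   The likely loss is therefore concentrated in mild or resolved events.

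3. **What happens to an event the data collector does see?** Section 4.14 has the data collector advise a clinic visit when a child is not improving. Section 5.4 has data collectors report to the data supervisors, who also receive reports under 4.17. A channel exists, but no adverse event form or duty is attached to it.

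4. **Whom does the visit reach?** Not every child. RDT refusals are not followed up (text after the exclusion criteria), the follow-up form needs consent at the visit (section 7), and section 4.3 expects 15% dropout. It is the only planned post-treatment contact with each followed child.

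5. **Size.** If a fraction r of events is reported, then observed proportion = true proportion × r. Purely as illustration, with assumed values:
   - True 10%, r from 0.30 to 0.80: 0.10 × 0.30 = 3% to 0.10 × 0.80 = 8%.
   - True 10% in both arms, r = 0.80 and 0.40: 8% against 4%, odds ratio (0.08/0.92) / (0.04/0.96) = about 2.1.

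   Nothing in the protocol supports these inputs. A head count is not possible either. The fever target is 1320 before dropout and 1518 after inflation, or 660 and 759 per arm. Those are febrile children, whereas the drug outcome counts treated children, and section 4.2 gives an antipyretic after a negative RDT.

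**The case against.** The strongest reply is that the visit lists are summaries. Both say what the information will include, the case report forms are still to be developed (4.9) and can change after the pilot (5.3), and current complaints already cover a persisting rash or infected finger. Serious events, the ones that matter most, are those most likely to reach a facility, where 4.17 does operate. The drugs are established first-line treatments, and both proportions sit under other outcome variables, neither primary nor secondary.

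Much of this stands, and it limits how serious the point is. It does not remove it. Section 4.17 states a rule for where events are tracked, and a better form alone would leave the data collector outside that rule.

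Four stronger readings are tempting, and the documents do not support them:
- **The data collector cannot report an event.** Section 5.4 links data collectors to the supervisors in the 4.17 chain; what is missing is an assigned duty.
- **The arms are captured differently.** Control CHWs refer suspected pneumonia and intervention CHWs give amoxicillin (4.2), so the worker who sees an antibiotic reaction may differ. But 4.17 applies the same two levels in both arms, section 6.2 lists no adverse-event comparison, and RDT events can arise in one arm only. Differential capture is possible, not shown.
- **CHWs will withhold reports.** Section 9.1 says "The misuse or the perception of misuse of medication or misclassification could cause their reputation to be tainted or harmed in the community". That describes a risk to the CHW and says nothing about under-reporting.
- **A child who is not improving is an unreported adverse event.** Section 3.5 already classes failure to clear symptoms as treatment failure.

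**Conclusion.** The point holds in a limited form. As written, the section 3.6 adverse-event proportions depend on spontaneous caregiver reports, and the visit best placed to ask has no listed question and no stated role in 4.17. Undercounting is likely, mainly of mild or resolved events. This rests on the ordinary assumption that not every caregiver reports every event unprompted. The amount cannot be estimated from the documents, and no between-arm bias is established. The change should be made before data collection starts, because resolved mild events cannot be recovered reliably afterwards. The primary outcomes are not affected.

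**What to change.** - **Day 5-7 form, both arms (4.14 and 5.1).** Add a short structured question on drug reactions since the CHW visit and, for children who had an RDT, on finger-prick events. Record onset, so that new events can be told apart from the presenting illness. This matters because some reactions listed for Coartem in 4.11.2, such as cough and anorexia, resemble that illness.
- **Section 4.17.** Name the data collector as a third reporting level who completes the adverse event form and informs the data supervisor. Align 4.14 and 5.1 with this.
- **Section 3.6 proportions.** Define them among followed-up children, with events from home visit, CHW and facility combined, and show the source of each event. List separately the events reported for children who were not visited, so that they are not lost.
- **Treatment failure.** Keep failure to improve under section 3.5 and do not count it as an adverse event by itself.

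Cost: a few questions at a visit already made by trained data collectors, with no new staff and no change to treatment or referral. The downsides are a slightly longer interview, a higher reported event rate, and some remaining overlap with illness symptoms.

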#### 4.18 Economic Analyses

The overall goal of the economic evaluation is to determine the cost effectiveness and the difference in economic costs between the use of RDTs in the diagnosis and treatment of malaria (the intervention) and the presumptive treatment of fever with Coartem (the control). The economic analysis will also determine the incremental cost-effectiveness of the use of RDTs in the diagnosis and treatment of malaria so as to provide an additional measure by which to judge the usefulness of the ZIMMAPS intervention. The economic analyses will be based both on cross sectional data collected from health facilities and data collected longitudinally from the caretakers of ill children. The key indicators will be direct economic costs incurred in both the treatment and control areas. We will measure such costs at the household, health care provider, and medical facility levels related to diagnosis and treatment of malaria and pneumonia by CHWs, including referrals. Health outcome will be measured as treatment failure defined earlier.

5. DATA COLLECTION AND MANAGEMENT

5.1 Data Collection

The effects of the intervention package will be collected through four main methods/activities:

#### Routine data collected from CHWs and facility-based records.

#### Performance assessments of CHW skills.

#### Follow-up visits of children treated by CHWs at home.

#### A set of household surveys.

CHWs will keep an outpatient department (OPD) register in which each person attended to will be registered. The OPD register will provide information on the name of the patient, address, sex, age or date of birth, date of onset of illness, main complaints, classification of the disease, drugs given, and comments (recovered, referred or died). The CHW will then make a monthly summary of the register. In addition, the CHW will keep a daily tally sheet for drugs and supplies dispensed and make a monthly summary. The CHW will keep a record of referred cases. The record (which is supplemented by information received from the health center) will include date and time of referral, presenting signs and symptoms (diagnosis), date and time seen at referred centre, date of discharge, and final diagnosis. The CHW will also complete an “identification and baseline form” for every child between six months and five years with fever or fast breathing. The health facilities in the area will keep morbidity and mortality records including information on all CHW referrals.

On a monthly basis the data collectors will visit the CHW and health facility and collect summaries of records kept in special design case report forms (CRFs). The information collected on CRFs for CHWs will include number of children seen, those classified as malaria or pneumonia or both, RDTs performed, drugs dispensed, referrals and whether a supervisory visit was made The information that will be collected on CRF at the health facility will include number of malaria and pneumonia cases, severe malaria and pneumonia cases, referrals from CHWs, deaths by cause, availability of RDTs, Coartem**®** and amoxicillin.

The data collectors will visit the CHWs at least every other day to collect completed identification and baseline forms to schedule a follow-up visit. The DC will check with the CHW register to ensure that every child seen by the CHW with fever of fast breathing has a completed identification and baseline form. The follow-up visits will be made at 5-7 days after the caregiver visits the CHW. Information that will be collected during the Day 5 – 7 follow-up visits will include, complaints that prompted heath seeking at the CHW, whether rapid diagnostic test was done, treatment given, counseling or advice given, self-reported adherence to the medication, outcome of the visitation, alternative treatment after the visit and where such alternative treatment was obtained, current general condition and complaints and results of temperature and respiratory rate taken.

Economic cost data from health facilities will be collected by the data collectors. These data will include the average costs associated with treating uncomplicated and severe cases of malaria and pneumonia, including overhead, equipment, personnel, medicines, and supplies. This information will then be matched with the case records in order to estimate the facility-based costs of treatment for children in intervention and control groups.

Household surveys will be conducted at the beginning (baseline), and at the end of the project to allow us measure some of the outcomes. These surveys will collect information on demography, care seeking behaviors, recent morbidity and mortality, preventive health measures especially for malaria, knowledge of danger signs, adherence to treatment, utilization and acceptability of CHW services, opinion about CHWs. Women resident in the study area aged 15 to 45 years who have at least one child under 5 years will be enrolled for this survey. One member per household will participate. Where there is more than one eligible member, the oldest will be selected. The data collectors will conduct the household surveys. This work will be independent of the follow-up visits. Eligible women will be enrolled based on the inclusion and exclusion criteria irrespective of whether they received care from a CHW or not. Women will be asked about the recent illnesses of their children, including about disease-specific symptoms, whether they sought care, what kind of care they sought, and what kind of treatment they received/followed. The post intervention household survey will also collect information on the acceptability of the intervention.

The CHWs and some opinion leaders in the communities will also be interviewed on their views on the intervention.

- 1. **Supervision of Data Collectors**

Supervision of data collectors will be achieved by assigning 6 DCs to a DS. The DS will visit and work with each of the assigned DC at least once every two weeks. The DS will watch the DC performing part of the assigned job followed by a discussion based on the observations and the DC’s general performance. Any DC whose performance consistently falls below average will be fired and replaced by one of the people on “shelf”.

The supervisors will make three types of supervisory visits

i. Scheduled visits

The Supervisor will visit a home at the same time as a DC, having made an appointment with DC

ii. Random unscheduled visits

The Supervisor will visit a DC unannounced and not by appointment. This visit will provide an opportunity for the supervisor to pick up any “bad” practices that may have cropped up in the course of the field work.

iii. Check visits

The Supervisor will visit a home on his own without the presence of the DC. This visit is performed for several reasons including:

- - - Obtain information from the home whether a reported visit by the DC was made
    - Find out about the conduct of the DC during the visit
    - Discuss any concerns of caregivers taking part in the study
    - Conduct a random blind interview - The supervisor conducts a repeat interview and compares the answers/responses with a similar interview conducted by a DC.

